### Outcomes {12}

The primary outcome is meeting one of the following treatment failure criteria within the first 120 h after birth:
Need for intubation and invasive mechanical ventilation for > 1 horFiO_2_ ≥ 50% for > 1 h after NICU admissionorpCO_2_ ≥ 70 mmHg in two consecutive blood gas analyses > 2 h apart

Secondary outcomes are:
Rates of invasive or less invasive surfactant administrationCumulative dose of surfactant in mg/kg birth weightRate of intubation and invasive mechanical ventilation within the first 120 h after birthDuration of invasive mechanical ventilation within the first 120 h of life (cumulative hours)Duration of invasive mechanical ventilation until PMA36 or death (cumulative hours)Duration of any respiratory support until PMA36 or death (cumulative days)Rate and severity distribution of BPDRate of discharge with supplemental oxygenRates of postnatal systemic dexamethasone and/or hydrocortisone intended for chronic lung diseaseRate of inhaled steroidsNeed for inotropes/vasopressors within the first 120 h of lifeNeed for steroids for treatment of arterial hypotension within the first 120 h of lifeMean FiO_2_ requirements within the first 120 h of lifeMean airway pressure within the first 120 h after birth

Further outcomes are:
Bayley Scales of Infant Development (3rd) Edition at 24 months corrected ageVisual assessment at 24 months corrected ageHearing assessment at 24 months corrected ageGMFCS-Score at 24 months corrected ageWechsler preschool and primary scale of intelligence (WPPSI-III) at 60 months corrected ageLung function at 60 months corrected ageMRI of the lung and brain at 60 months

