**Outcome assessment**									
BPD					●				
Death					●				●
ROP					●				
NEC					●				
FIP					●				
PDA					●				
Nosocomial infections					●				
Brain injury (CUS)				●	●				
Feeding data					●				
Inotropes					●				
Postnatal steroids						●			
Bayley III/GMFCS							●		
Visual and hearing							●		
Lung function								●	
WPPSI-III								●	
Lung/brain MRI								●	
Parental questionnaire	Every 3 months after discharge								

*BPD* bronchopulmonary dysplasia, *CUS* cerebral ultrasound, *FIP* focal intestinal perforation, *GMFCS* gross motor function classification scale, *MRI* magnetic resonance imaging, *NEC* necrotizing enterocolitis, *PDA* persistent ductus arteriosus, *PMA* postmenstrual age, *ROP* retinopathy of prematurity

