The analysis of the primary endpoint will be done by Cochran-Mantel-Haenszel test stratified for treatment groups. The primary endpoint will be re-evaluated by Cochran-Mantel-Haenszel test adjusted for gestational age group (26 + 0–27 + 6 versus 28 + 0–29 + 6 weeks) and center. If the final number of centers does not allow adjustment for single centers, centers will be grouped. The grouping of centers will be justified within the statistical analysis plan. All secondary endpoints will be compared by Cochran-Mantel-Haenszel test or Student’s *t* test. In case of non-normally distributed data, Student’s *t* test will be replaced by Wilcoxon-Mann-Whitney test. The distribution of severity of BPD will be compared between the treatment groups by generalized logit model. Clinical and demographic characteristics of maternal and neonatal data will be described by mean and standard deviation, median, quartiles and minimum/maximum or rate and percentage. The analysis of the follow-up endpoints will be specified in an amendment to the study protocol before start of the 2- and 5-year follow-up. In case of more than 10% missing values concerning the primary endpoint, a worst case/best case analysis for this endpoint will be performed in the intention to treat population as sensitivity analyses and results will be included into the final report. No sensitivity analyses will be done for secondary or further relevant endpoints. In case of more than 20% missing values concerning one of the endpoints until PMA36, this endpoint will only be tabulated but no statistical test will be performed due to risk of biased data.

All analyses will be predefined in a statistical analysis plan written before end of study and completion of data monitoring. Only the analysis of the primary outcome variable in the intention-to-treat population will be considered confirmatory on a level of significance of 0.05. All other analyses including the analysis of the primary outcome variable in the per protocol population and all analyses concerning secondary endpoints will be considered exploratory only.

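### Respiratory-support and ventilation time stop counting at death, and BPD gives death no role, so unequal mortality could distort these exploratory lung outcomes

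*Protocol article*

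**What the plan says.** Outcomes {12} lists among the secondary outcomes "Duration of any respiratory support until PMA36 or death (cumulative days" and "Duration of invasive mechanical ventilation until PMA36 or death (cumulative hours", both cumulative totals that end at death. It also lists the rate and severity distribution of BPD, with no composite with death and no category for death. Table 1 marks BPD at the PMA 36 visit only. Death has a separate row, marked at PMA 36 and at the end of the study.

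Statistical analysis {20a} fixes the methods. "All secondary endpoints will be compared by Cochran-Mantel-Haenszel test" or t test, with the Wilcoxon-Mann-Whitney test replacing the t test for non-normal data. The t and Wilcoxon tests are unstratified, and no strata are named for the secondary Cochran-Mantel-Haenszel tests. For BPD severity, "The distribution of severity of BPD will be compared between the treatment groups by generalized logit model". None of these comes with a rule for infants who die.

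The same section says "No sensitivity analyses will be done for secondary or further relevant endpoints". It has a tabulate-only rule, which opens "In case of more than 20% missing values concerning one of the endpoints until PMA36", but does not say whether death counts as missing. All secondary analyses are declared exploratory. Death before discharge is an expected serious adverse event reported by arm, and deaths are to be evaluated with 95% confidence limits for both groups (Adverse event reporting and harms {22}).

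**The concern.** Ending the count at death can only remove time from an infant's total. An infant on support who dies on day 3 contributes at most 3 days of respiratory support, a low and therefore favourable value. If one arm has more early deaths, that arm can show shorter support with no benefit in survivors. BPD can be affected similarly, because an infant who dies before PMA36 cannot be recorded with BPD at that visit.

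The protocol treats unequal mortality as a live possibility. Its Discussion cites a trial of sustained inflation that found no difference in BPD but more deaths, and excess mortality in the treatment group is a ground for stopping the trial. The Abstract names less chronic lung disease as the eventual aim, so readers will look at these outcomes even though they are exploratory.

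**Working it through.** **The plan's own figures.** The article gives no mortality rate, BPD rate or mean duration, so there is no stated figure on this point to reproduce. Its 103 per group reproduces with a continuity-corrected two-proportion formula (50% v 30%, two-sided 0.05, power 80%). It is used below only as the arm size.

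**Window.** With PMA36 taken as 36+0 weeks (252 days), birth at 26+0 (182 days) leaves 252 − 182 = 70 days, and birth at 29+6 (209 days) leaves 252 − 209 = 43 days.

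**Respiratory-support days.** Let S be the mean in survivors (the same in both arms, so no true effect), t the time counted in infants who die, and d the death rate. An arm's mean is (1 − d)S + d·t, so the difference, higher-death arm minus lower-death arm, is (d_high − d_low)(t − S). All inputs are assumptions.
- 5-point excess, S = 35, t = 3: 0.05 × (3 − 35) = −1.6 days.
- 5-point excess, S = 35, t = 10: 0.05 × (10 − 35) = −1.25 days.
- Extremes for S = 25 to 45 and t = 3 to 10: 0.05 × (10 − 25) = −0.75 and 0.05 × (3 − 45) = −2.1 days.
- Wider set, S = 30 to 50 and t = 3 to 20: −0.5 to −2.35 days for a 5-point excess, −1.0 to −4.7 for 10 points. The longest means are generous, given a 43-day window in the most mature infants.
- Late deaths, S = 30, t = 40: 0.05 × (40 − 30) = +0.5 day, or +1.0 for 10 points. The sign changes.
- Equal mortality: the first factor is zero, so there is no difference.

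**Simulation.** 2,000 trials, 103 per arm. Survivor support is gamma-distributed (shape 2, scale 17 days), time to death is exponential with mean 10 days, both are capped at 56 days, and there is no effect in survivors.

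| Deaths | Mean difference (days) | Trials with lower mean in the higher-death arm | Chance that an infant in the higher-death arm has the worse value: as defined | Same, death ranked worst |
|---|---|---|---|---|
| 5% v 5% | 0.0 | 49% | 0.50 | 0.50 |
| 5% v 10% | −1.0 | 67% | 0.48 | 0.52 |
| 5% v 15% | −2.1 | 81% | 0.46 | 0.55 |

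Ranking death worst reverses the direction.

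**BPD.** Assume 5% v 10% deaths, a BPD risk of 25% in infants who would survive in either arm, and 50% in the 5% who die in one arm only.
- BPD cases per infant randomized: lower-death arm 0.90 × 0.25 + 0.05 × 0.50 = 0.250; higher-death arm 0.90 × 0.25 = 0.225.
- Survivors as denominator: 0.250/0.95 = 26.3% v 0.225/0.90 = 25.0%.
- All infants as denominator: 25.0% v 22.5%.
- BPD or death: 25.0 + 5 = 30.0% v 22.5 + 10 = 32.5%, the reverse.
- If the infants who die have the same 25% risk, the survivor comparison is 25.0% v 25.0% (no bias), but the all-infant comparison is still 23.75% v 22.5%. If their risk is only 15%, survivors show 24.5% v 25.0%, slightly the other way.

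**Invasive-ventilation hours.** The same formula with a 5-point excess, H hours in survivors and h in infants who die, gives 0.05 × (h − H). With H = 200 and h = 24 this is −8.8 h; with H = 40 and h = 72, +1.6 h; with H = 40 and h = 480, +22 h. The direction depends on who accrued more hours.

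**The case against.** A reader might infer that the arm with more deaths must look better on all three outcomes. The documents do not support that.

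- **Ventilation hours.** Sample size {14} expects primary endpoints in 50% (control) and 30% (intervention), and ventilation for more than 1 h is only one component. So at least 50% and 70% of infants should not have ventilation beyond 1 h in the first 120 h. An infant ventilated until death on day 3 has up to 72 h and would rank worse than most, unless much ventilation starts after 120 h. This objection stands.
- **BPD.** The article gives no BPD definition or denominator. That infants who die drop out is an inference from Table 1, and the survivor-only bias needs deaths in higher-risk infants. This stands, but either denominator leaves death without a role, and the outcome list itself fixes BPD without one.
- **Lack of adjustment.** Randomization is stratified by center and gestational age, so unequal windows to PMA36 are roughly balanced. An unadjusted test costs mainly precision and is not a source of bias here.
- **Size.** Mortality and durations are assumed. With an assumed SD of 15 to 20 days and 103 per arm, the standard error of a mean difference is SD × √(2/103), about 2.1 to 2.8 days, so a shift of 1.25 to 1.6 days is below one standard error.
- **Status.** These outcomes are exploratory, none is designated key, and deaths are reported by arm. A while-alive duration is also a legitimate definition if labelled as such. This limits the consequence, but separate reporting of deaths does not correct the comparisons.

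Leaving details to the SAP answers little here: the protocol itself fixes the definitions and excludes sensitivity analyses for these endpoints.

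**Conclusion.** The point holds, conditionally on unequal mortality. For respiratory-support days, early deaths make the arm with more deaths look better by about 1.25 to 1.6 days per 5 points of excess mortality (survivor mean 35 days, death on days 3 to 10; 0.75 to 2.1 for survivor means of 25 to 45). Deaths later than the survivor mean change the sign, and equal mortality gives no between-arm bias. For BPD, the arm with more deaths can look better if those who die are at higher BPD risk, or if all infants are the denominator. For invasive-ventilation hours no direction can be claimed, but the comparison still mixes death with benefit.

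It would go too far to say that mortality is concealed or that the trial's main conclusion is at risk: deaths are shown by arm, and the confirmatory primary analysis is unaffected. The change is worth making because it is cheap and these outcomes bear on the trial's eventual aim.

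**What to change.** Add the following as exploratory analyses:
- Days alive and free of respiratory support to PMA36, and likewise of invasive ventilation, with death before PMA36 scored 0 or ranked worst. Compare by a rank test stratified by the randomization strata (gestational-age group and center, with centers grouped if needed).
- BPD or death before PMA36.
- Death as a category in the BPD severity comparison.

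Keep the present durations as descriptive results, with mortality by arm beside them. State the BPD denominator and whether death counts as missing under the 20% rule.

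Cost: SAP wording plus a short protocol amendment, because the outcome list and the exclusion of sensitivity analyses stand in the protocol and changes go to the Ethics Committees ({25}). No new data are needed: death, BPD and ventilation data are already scheduled in Table 1. The downside is that support-free days and composites are less direct to interpret than plain durations or BPD alone.

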### Participant timeline {13}

#### Study procedures, examination methods, and outcome assessment

The description of the study procedures and examinations are shown in Fig. 1. A summary of important outcomes and time points of assessment are shown in Table 1. A detailed description of the study process for the individual patient is summarized in Fig. 2.

**Fig. 1 Fig1:**
[figure not shown]
Overview about the study procedures and examinations. IC, informed consent; CUS, cerebral ultrasound; MRI, magnetic resonance imaging; PMA, postmenstrual age

**Table 1 Tab1:** Time points of interventions and outcome assessment of outcomes during the study

Points of action	Screening	Baseline	Visits			End of inpatient study	Follow-up		End of study
Visit	1	2	3	4	5	6	7	8	9
Time point/age	Prior birth	0 h	120 h	Day 7	PMA 36	Discharge	24 months corrected age	60 months of age	
Inclusion criteria	●								
Exclusion criteria	●								
Informed consent	●								
**Neonatal and maternal characteristics**									
Data		●							
**Study intervention/ventilation**									
Start		●							
End			●						
PEEP data			●						
Surfactant treatment			●						
Ventilation data			●		●	●			
**Safety**									
Serious adverse events	Continuous reporting until discharge								
**Outcome assessment**									
BPD					●				
Death					●				●
ROP					●				
NEC					●				
FIP					●				
PDA					●				
Nosocomial infections					●				
Brain injury (CUS)				●	●				
Feeding data					●				
Inotropes					●				
Postnatal steroids						●			
Bayley III/GMFCS							●		
Visual and hearing							●		
Lung function								●	
WPPSI-III								●	
Lung/brain MRI								●	
Parental questionnaire	Every 3 months after discharge								

*BPD* bronchopulmonary dysplasia, *CUS* cerebral ultrasound, *FIP* focal intestinal perforation, *GMFCS* gross motor function classification scale, *MRI* magnetic resonance imaging, *NEC* necrotizing enterocolitis, *PDA* persistent ductus arteriosus, *PMA* postmenstrual age, *ROP* retinopathy of prematurity

**Fig. 2 Fig2:**
[figure not shown]
Study process for the individual patient

### Sample size {14}

Based on a pre-study survey among participating centers and the results of the AMV study [14], we expect 50% primary endpoints within the control group (lower PEEP level). The intervention will be regarded as being successful if it lowers the rate of the primary endpoints to 30%. This follows the expectations within similar studies [15]. To lower the rate of primary endpoints from 50 to 30% and to confirm this via Cochran-Mantel-Haenszel test (level of significance = 0.05, power = 80%), a sample size of 103 patients per group will be needed. To account for 5% drop outs, an overall sample size of 216 patients have to be recruited and treated within the study.

### Recruitment {15}

#### Recruitment and study duration

Patients will be recruited in 6 German tertiary care neonatal centers. Results of a systematic surveillance protocol prior to study start yielded a number of 240 eligible preterm infants meeting the inclusion criteria annually in all participating centers. Based on the assumption that approximately 50% of eligible infants will be included in the study, the recruitment period is expected to be 27 months. All preterm infants who are born at the participating institutions with a gestational age at birth of 26 + 0/7 to 29 + 6/7 weeks have to be screened for the study. Each screened patient is given a patient screening number (PSN) in consecutive order according to the screening log in the investigator site file (ISF). This number is the overall identifier of the pseudonymized patient throughout the study. For every screened patient, a screening form has to be filled in the electronic case report form (eCRF). This enables the documentation of non-biased recruitment. The screening eCRF form will document presence and absence of inclusion and exclusion criteria, whether the parents had been approached and whether informed consent was given, but will not document any patient identifiers. Outborn infants will not be screened as study treatment has to start immediately after birth. Patients can only be enrolled into the study if informed written consent was given by both parents/guardians (by the only parent/guardian in case of single-parent/guardian families) before birth. In case parents are less than 18 years of age, the relevant legal guardian(s) of the child has/have to sign the informed consent. Following multiple birth, parents are asked whether the infants could be randomized separately. If parents wish randomization to one study arm, the second child is treated like the randomized child, but not recruited to the study. The parental wish is documented on the informed consent form.

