## Assignment of interventions: allocation

### Sequence generation {16a}

#### Randomization and allocation concealment

Infants will be randomly assigned in a 1:1 ratio with variable block sizes. Randomization lists will be stratified by center and gestational age (26 + 0–27 + 6 and 28 + 0–29 + 6 weeks). Sequentially numbered, sealed, opaque envelopes indicating the study group will be prepared. Provision of randomization envelopes will be done by an independent institution not involved in patient recruitment.

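### Siblings can be randomised separately, but the confirmatory test uses neither the family link nor the randomisation strata: it is valid, with a modest loss of efficiency

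*Protocol article*

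**What the plan says.** All of this is in the protocol article.

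- **Entry of siblings** (Recruitment and study duration): after a multiple birth, "parents are asked whether the infants could be randomized separately". If the parents want one arm for both, "the second child is treated like the randomized child, but not recruited to the study". So a pair is in the data set only when each infant has its own allocation.
- **Allocation** (Sequence generation {16a}): "Infants will be randomly assigned in a 1:1 ratio with variable block sizes", and "Randomization lists will be stratified by center and gestational age". Family is not a stratum.
- **Primary analysis** (Statistical analysis {20a}): "The analysis of the primary endpoint will be done by Cochran-Mantel-Haenszel test stratified for treatment groups". The strata follow in a second step: "The primary endpoint will be re-evaluated by Cochran-Mantel-Haenszel test adjusted for gestational age group" and for centre. Only the intention-to-treat analysis of the primary outcome is confirmatory.
- **Other endpoints** (same section): "All secondary endpoints will be compared by Cochran-Mantel-Haenszel test or Student’s" t test, with Wilcoxon-Mann-Whitney for non-normal data and a generalized logit model for BPD severity. Follow-up endpoints are left to a later amendment.
- **Sample size {14}**: 50% against 30%, significance level 0.05, power 80%, 103 per group, 216 in all. The calculation counts single infants.

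No section mentions correlation between siblings.

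**The concern.** Siblings share a mother, a gestational age, a centre and a care team, so their outcomes are likely to be correlated. A pair split between the arms is a partly matched comparison. An analysis that knows the link can give that comparison more weight; the CMH, t test and Wilcoxon test cannot.

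The primary wording raises a related matter. Treatment is what the test compares, so stratifying for treatment groups names no stratum. Read together with the next sentence, the confirmatory CMH leaves out gestational age group and centre, although randomisation was stratified on both. At stake is precision that the trial could have at almost no cost, not the validity of its result.

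**Working it through.** **The plan's own figure.** Two-sided 0.05, power 80%, 50% against 30%:

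n = [1.960·√(2·0.4·0.6) + 0.842·√(0.25 + 0.21)]² / 0.2² = 93.0 per group. With continuity correction, (n/4)·[1 + √(1 + 4/(0.2n))]² = 102.8, so 103, as stated. Then 206/0.95 = 216.8, against 216 stated, which agrees to within one infant. Without continuity correction, 103 per group has 83.9% power.

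**Inputs for siblings.** The documents give none of these, so they are assumptions: f, the share of infants in twin pairs; ρ, the sibling correlation of the binary outcome; c, the chance that both twins land in the same arm. Independent allocation gives c = 0.5. Simulated blocks of 4 and 6 give c of about 0.4, because siblings drawing from the same block tend to be split.

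**Formulas.**

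- True variance relative to that assumed by a test that ignores pairs: 1 + fρ(2c − 1).
- Information with optimal weighting: (1 − f) + f·[(1 − c)/(1 − ρ) + c/(1 + ρ)].

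With c = 0.5 the variance ratio is exactly 1, so type I error is 5.0% for any f and ρ. For f = 0.3, ρ = 0.3, c = 0.4, the ratio is 1 + 0.09·(−0.2) = 0.982, and the information is 0.7 + 0.3·(0.6/0.7 + 0.4/1.3) = 1.049.

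Results for c = 0.4 and 103 per group, no continuity correction:

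| f | ρ | Variance ratio | Type I error | Information | Power, pairs ignored | Power, pairs used | Gain (points) |
|---|---|---|---|---|---|---|---|
| 0.20 | 0.2 | 0.992 | 4.9% | 1.017 | 84.0% | 84.5% | 0.5 |
| 0.20 | 0.3 | 0.988 | 4.9% | 1.033 | 84.1% | 85.1% | 1.0 |
| 0.30 | 0.3 | 0.982 | 4.8% | 1.049 | 84.1% | 85.6% | 1.5 |
| 0.30 | 0.5 | 0.970 | 4.7% | 1.140 | 84.3% | 88.4% | 4.1 |
| 0.35 | 0.5 | 0.965 | 4.6% | 1.163 | 84.3% | 89.0% | 4.7 |

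**Simulation of the sibling effect.** 206 infants, 12 strata (6 centres by 2 gestational age groups), blocks of 4 or 6, 2,500 runs per setting. The comparison is the stratified CMH without continuity correction against least squares with stratum effects and exchangeable sibling correlation:

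| f | ρ | Type I error, CMH | Type I error, pair-aware | Power, CMH | Power, pair-aware | Gain (points) |
|---|---|---|---|---|---|---|
| 0 | – | 5.4% | 5.6% | 83.2% | 83.8% | 0.6 |
| 0.2 | 0.3 | 5.2% | 5.4% | 83.5% | 84.6% | 1.1 |
| 0.3 | 0.3 | 4.8% | 5.1% | 83.1% | 84.4% | 1.3 |
| 0.3 | 0.5 | 4.4% | 4.9% | 83.4% | 85.6% | 2.1 |
| 0.4 | 0.5 | 4.4% | 4.8% | 83.8% | 86.2% | 2.4 |

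Gains are taken from unrounded values.

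**Simulation with prognostic strata.** With assumed centre and gestational age effects, 20% or 35% of infants in pairs and a correlation of about 0.22-0.47 (2,000 runs per setting), the results were:

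- Type I error: unstratified CMH 3.7-3.9%, stratified CMH 4.9-5.0%, pair-aware model 5.0-5.3%.
- Power: 84.5-85.7%, 86.6-87.9% and 87.4-91.2% respectively. Modelling siblings added 0.6 to 4.5 points over the stratified CMH.

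A further simulation of the same kind gave about 2-3 points from stratifying and 1-2.5 from modelling siblings. The low type I error of the unstratified CMH here comes mostly from leaving out the strata, so it is not evidence about siblings.

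**The case against.** The strongest case against is that nothing is broken. The test is valid, the protocol recruits only one infant when parents want a single arm, and the planned power is met. Choosing a valid test that is not the most efficient is then a preference, and a sibling-aware sensitivity analysis is the kind of detail that a statistical analysis plan may hold. Much of this stands. A reader might infer that standard errors are wrong or that false positives rise. The design does not support that: with allocation by infant, the variance is right or slightly overstated. A reader might also infer that the trial misses its 80%. The uncorrected CMH has 83-84% in the first simulation. With continuity correction it has 79.5-79.9% with siblings and 79.0% without, so siblings do not lower it.

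The size of the gain is also open to challenge. It rests on assumed inputs. The Monte Carlo error of one power estimate from 2,500 runs is √(0.83·0.17/2500), about 0.75 points, although less for differences within the same runs. The pair-aware test gained 0.6 points even with no siblings, with a slightly higher type I error, so part of the simulated gain is a difference in test size. The gain from stratifying also depends on prognostic strata: in the first set of block simulations, stratified and unstratified power were practically equal (83.4% each at f = 0.3, ρ = 0.5).

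What does not stand is that this is only missing detail. The protocol itself fixes the confirmatory method, and what it explicitly leaves to the analysis plan for the primary test is the grouping of centres.

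**Conclusion.** The point holds as one of efficiency. Separately randomised siblings enter the data, no test named for endpoints up to 36 weeks has a family term, and the confirmatory CMH takes in the randomisation strata only at re-evaluation. Type I error is near or slightly below 5%, and the 80% target is safe.

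For 20-35% of infants in twin pairs and a sibling correlation of about 0.2-0.5, the loss from ignoring siblings is about 1 to 2.5 points of power, under 1 at the bottom of the range and about 4 to 5 at the top. Leaving out the strata costs roughly a further 2 to 3 points if centre and gestational age group are prognostic. It would go too far to say that every planned analysis is affected, because the follow-up analyses have yet to be specified.

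**What to change.** - Make the CMH stratified by gestational age group and centre (grouped if needed, as already foreseen) the single confirmatory test, and correct the phrase about stratification for treatment groups.
- Confirm that the database holds a family identifier linking siblings. The article describes only a patient screening number; the full case report form is not shown.
- Prespecify beside the CMH a strata-adjusted treatment estimate that accounts for siblings, for example GEE with exchangeable working correlation clustered on the mother, for the primary and the secondary endpoints. State that it does not replace the confirmatory test, so that it offers no second chance at significance. GEE is the safer choice here: with most families contributing one infant, a logistic model with a random intercept for the mother can be poorly identified and estimates a conditional effect.

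The cost is a change of wording before the data are analysed, one linking variable and one extra model-based analysis. No additional infants are needed, and treatment is not touched.
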